### Sample size

To calculate the sample size of the CT and IPT group, we combined rudimentary findings from previous randomised trials, which resulted in a mean relapse/recurrence rate of 33% after two years of follow-up, compared to 67% following antidepressant medication and/or clinical management [28,29,31-33]. Based on these results, we assume a difference of 20% in relapse between CT and IPT. Using survival analysis (two-sided, α = 0.05, power = 80%), we calculated that 75 patients per treatment condition would suffice to detect this statistically significant difference rate in relapse/recurrence between the two conditions in the long term.

A waiting list condition is included to investigate whether the effects of CT and IPT exceed the outcome in patients who do not receive treatment, a finding that has been demonstrated in numerous previous studies [60-63]. A power calculation showed that 30 participants in the waiting list condition will be sufficient to detect a statistically significant difference between the two active conditions combined (CT and IPT) and the waiting list after eight weeks.

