### Randomisation and procedure

Eligible participants will be contacted by telephone for a baseline visit at the university. Preceding this initial visit to the research centre, participants will receive an appointment letter, including study information. This will allow them to consider their study participation well before they agree to participate (approximately one week). Furthermore, to decrease the burden of the first assessment, participants will be asked to already fill out a substantial part of the baseline questionnaires at home. Randomisation will take place after informed consent is obtained and the second part of the baseline questionnaires are filled out. In our design we prestratified groups by first (1 episode) and recurrent (> 1 episodes) depression. The researcher will press the 'assign' button on the computer screen, after which the database randomly allocates the participant to one of the treatment conditions (CT or IPT), or to the waiting list condition by using block randomisation. This waiting list condition is included because it has been frequently argued in psychotherapy research that the effect in treatment studies cannot be attributed to the intervention(s) that are studied, unless a placebo or no-treatment group is included [65]. With regard to the nature of the treatments, blinding of the participants and researchers is not possible.

In reporting the follow-up period of the CT and IPT condition in this study, we distinguish three phases; (a) the Treatment phase (baseline to 7 months); the period when therapy will be delivered; (b) The Trial follow-up phase (month 8-12) in which depression severity will be measured monthly; and (c) The Long-term follow-up phase (12 to 24 months); the period covered by retrospective assessment. All questionnaires will be administered on a computer. Pre- and post treatment assessment (baseline and 7 months) will take place at the University. All other follow-up self-report assessments will take place at home via the internet at three, eight, nine, ten, eleven, twelve and twenty-four months after inclusion.

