Although the baseline assessment is the same, the follow-up period of the waiting list condition is somewhat different as compared to the CT and IPT condition (see Figure 1). Participants in this condition will be measured less often, and at different points in time. The treatment phase of the participants in this condition does not start immediately after baseline, but after an 8-week waiting list period. To be able to investigate the effect of this waiting period, and to mark the starting point of the treatment phase, a second identical baseline assessment will take place two months after the initial baseline assessment. As a consequence, the post-treatment assessment in this condition will take place after nine months (instead of after seven months in the CT and IPT condition). Furthermore, patients in this condition will only have two more assessment after their post-treatment measure. This will take place at 14 and 26 months, and is identical to the 12 and 24 months assessment of the CT and IPT condition. To summarize, patients in the waiting list condition will have the same baseline assessment as compared to participants in the CT and IPT condition. However, they will have a second baseline assessment at two months follow-up, and their 9, 14, and 26 month follow-up assessments will parallel respectively the 7, 12, and 24 months assessments of the CT and IPT group (see table 1).

**Table 1 T1:** Overview of instruments per time point in the CT and IPT group*

Instrument	0**	3	7	8-11	12	24
						
*Clinical Outcome measures*						
Beck Depression Inventory II	**•**	**•**	**•**	**•**	**•**	**•**
Quick Inventory of Depressive symptoms	**•**				**•**	
Brief Symptom Inventory	**•**		**•**		**•**	**•**
Diagnostic Interview for Depression		**•**	**•**	**•**	**•**	**•**
Beck Hopelessness Scale	**•**		**•**			
Longitudinal Interval Follow-up Evaluation						**•**
						
*Process variables*						
Attributional Style questionnaire	**•**	**•**	**•**		**•**	
Dysfunctional Attitude Scale	**•**	**•**	**•**		**•**	
Inventory of Interpersonal Problems	**•**	**•**	**•**		**•**	**•**
Leiden Index of Depression Severity	**•**	**•**	**•**			
Ruminative Response Scale NL	**•**	**•**	**•**			
Self-Liking and Self-Competence Scale	**•**	**•**	**•**			
Single Category Implicit Association Task	**•**		**•**			
						
*Economic Evaluation measures*						
Health care use Questionnaire	**•**	**•**	**•**		**•**	**•**

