Productivity and Disease Questionnaire	**•**		**•**		**•**	**•**
Work and Social Adjustment Scale	**•**		**•**		**•**	**•**
Euroqol-6D	**•**		**•**		**•**	**•**
Rand 36	**•**		**•**		**•**	**•**
						
*Other measures*	**•**					
Genetic information						
Working Alliance Inventory		**•**				
Collaborative Study Psychotherapy Rating Scale	**•**	**•**	**•*****			
Working Alliance Inventory-short observer version	**•**	**•**	**•*****			

* Patients in the waiting list condition will receive the same baseline assessment, they will have a second baseline assessment at 2 months follow-up, and their 9, 14, and 26 month follow-up assessments parallel respectively the 7, 12, and 24 month assessments of the CT and IPT group. ** The following general predictors will be administered at baseline as well: demographic variables, family anamnesis, childhood experiences, life-events, reliability and expectations. *** During the treatment phase, all sessions will be videotaped. Only a random selection of tapes will be rated.

In all conditions a BDI-II will be filled out before each session during the treatment phase. After the two-year follow-up period, a modified version of the semi-structured Longitudinal Interval Follow-Up Evaluation (LIFE) [66] will be administered to retrospectively map out the course of depressive symptoms. To optimize the adherence of self-report assessments, participants will receive an email foregoing each assessment point. If one does not complete the questionnaires within one week, an email-reminder will be sent. If the participant still fails to fill out the questionnaires, a phone call will be made.

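### The CT+IPT versus waiting-list comparison is set at eight weeks, but CT and IPT have no scheduled assessment between baseline and month 3

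*Protocol article*

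**What the plan says.** The Sample size section gives the purpose of the third arm: "A waiting list condition is included to investigate whether the effects of CT and IPT exceed the outcome in patients who do not receive treatment". It then states: "A power calculation showed that 30 participants in the waiting list condition will be sufficient" to detect a "difference between the two active conditions combined (CT and IPT) and the waiting list after eight weeks". The Design section gives 75 CT, 75 IPT and 30 waiting-list participants, and says that the waiting list starts treatment after its eight-week wait.

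The Randomisation and procedure section gives the waiting list its eight-week measurement: "a second identical baseline assessment will take place two months after the initial baseline assessment". For CT and IPT, the same section places the pre- and post-treatment assessments at baseline and 7 months, and all the others "at home via the internet at three, eight, nine, ten, eleven, twelve and twenty-four months after inclusion". The Abstract and Table 1 give the same CT and IPT schedule.

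One further source of data lies between baseline and month 3: "In all conditions a BDI-II will be filled out before each session during the treatment phase". The Interventions section sets 12 to 20 sessions, depending on individual progress. The article does not say which measurement represents CT and IPT at week 8.

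**The concern.** A comparison fixed at eight weeks needs a score at about eight weeks in every arm. Here one side has a scheduled assessment for every participant, and the other side has none. Near week 8 an active-arm patient has a BDI-II only if he or she attends a session then, and the session number reached will vary between patients. Patients who have stopped attending have no form, so any selection by attendance falls on the active side alone.

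The contrast matters because it is the only one with untreated patients. The first research question asks whether CT and IPT are effective and whether one is superior. The stated hypothesis is that the two are similar, so a head-to-head result cannot answer the first half. The Randomisation and procedure section itself justifies the arm on the ground that effects cannot be attributed to treatment without a placebo or no-treatment group.

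**Working it through.** **1. The schedules side by side** (Randomisation and procedure; Table 1 and its footnote)

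| Month | CT and IPT | Waiting list |
|---|---|---|
| 0 | baseline | baseline |
| 2 (week 8) | nothing scheduled; session BDI-II for attenders | second full baseline |
| 3 | internet assessment | nothing scheduled; treatment due to have begun |
| 7 | post-treatment | nothing scheduled |
| 9 | monthly follow-up | post-treatment |

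The later waiting-list assessments are at 14 and 26 months, against 10, 11, 12 and 24 months in CT and IPT. After baseline the only shared month is month 9, by which time the waiting list has been treated. No scheduled assessment is shared while the waiting list is untreated. The three-group chi-square tests in the Analyses section give no substitute at post-treatment, for the same reason.

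**2. The plan's own figure.** The 30 cannot be reproduced, because no effect size, SD, alpha or power is stated for this contrast. Alpha 0.05 two-sided and 80% power are stated for the relapse calculation; I assume them here.

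- Standard error in SD units: √(1/150 + 1/30) = √0.04 = 0.20.
- Detectable d at 80% power: (1.960 + 0.842) × 0.20 = 0.56.
- Detectable d at 90% power: (1.960 + 1.282) × 0.20 = 0.65.

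**3. Does losing active-arm scores cost power?** Detectable d at 80% power is 2.80 × √(1/30 + 1/n), where n is the number of active patients with a usable score.

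| Share of 150 available | n | Detectable d |
|---|---|---|
| 100% | 150 | 0.56 |
| 90% | 135 | 0.565 |
| 80% | 120 | 0.57 |
| 70% | 105 | 0.58 |
| 60% | 90 | 0.59 |

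Power is hardly affected, because the 30 waiting-list patients dominate the standard error. What remains is bias.

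**4. Illustration: timing.** Suppose raw month-3 active scores (13 weeks) were set against week-8 waiting-list scores. Let g be the natural improvement, in SD, over the extra 5 weeks, with no treatment effect. Two-sided type I error is 1 − Φ(1.96 − g/0.20) + Φ(−1.96 − g/0.20).

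- g = 0.1: 0.08
- g = 0.2: 0.17
- g = 0.3: 0.32

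If instead a true treatment effect grew linearly from baseline, it would be multiplied by 13/8 = 1.625. A week-8 d of 0.3, 0.4 or 0.5 would appear as 0.49, 0.65 or 0.81.

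**5. Illustration: attendance.** Suppose a fraction m of active patients has no session form near week 8, and their mean differs from that of attenders by δ SD. Using attenders only then shifts the active mean by m × δ. At an assumed m of 15% to 25% (about 22 to 38 of 150), a shift of 0.1 SD needs δ = 0.1/0.15 = 0.67 down to 0.1/0.25 = 0.40. The sign is unknown: patients may stop because they do badly or because they have improved.

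The values of g, m and δ and the linear growth are assumptions. The article gives none of them.

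**The case against.** The strongest reply is that the active arms are not short of BDI-II data around week 8. They have a baseline score, session scores and a month-3 score. The month-3 form is completed at home by internet, with an e-mail reminder and a telephone call, so it does not depend on attendance. The Analyses section lists intention-to-treat and multilevel analyses. A multilevel model on actual assessment dates could estimate the active mean at week 8 and keep patients who stop therapy, through their baseline, early-session and month-3 scores. Naming the window and the model is commonly left to an analysis plan.

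Much of this stands. A reader might infer that the contrast will compare month 3 with month 2, or that it must drop patients who leave therapy. The article states neither. The figures in steps 4 and 5 of the working show what such analyses would do; they do not describe a planned one.

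A reader might also infer that mediation is compromised, since the waiting list repeats the whole battery at two months while CT and IPT have no process scores then. The article plans mediation as CT against IPT, and most process scales are shared by those arms at 0, 3 and 7 months. No mediation test against the waiting list is stated, so no stated aim is lost.

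What does not stand is that the matter is only analysis detail. A model can interpolate a week-8 value for a patient who has stopped attending, but it cannot supply one. It needs missing-at-random and curve-shape assumptions on the active side, whereas the waiting list has a direct measurement. The schedule is stated in full in three places, so the missing assessment is not something that condensing the protocol would explain. Figure 1 was not available for this review, but the text and Table 1 agree.

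**Conclusion.** The point holds as a mismatch between a powered time point and the assessment schedule. The only comparison with no treatment is set at eight weeks, and CT and IPT are not measured then by schedule. Their week-8 value must come from attendance-dependent forms or from a model. A raw month-3 versus month-2 comparison would favour treatment if untreated patients improve over time.

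The documents alone do not fix the size of any bias. Under the assumed drifts, the unadjusted timing error could raise type I error to between 0.08 and 0.32; a well-specified model would do much better. Power is not the issue, and the adequacy of 30 cannot be judged without the effect size that was assumed.

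The reach is limited. Only the effectiveness half of research question 1 is weakened; the CT-versus-IPT, relapse and mediation aims are not. The Sample size section also describes superiority over no treatment as already shown in many studies, so the contrast is confirmatory. This is a should-fix: a cheap improvement, and best made before data collection because a week-8 score that was not collected cannot be recovered.

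**What to change.** Send the internet BDI-II to all CT and IPT participants 8 weeks after baseline, whether or not they still attend sessions, through the existing e-mail, reminder and telephone procedure. Add the assessment to the Randomisation and procedure section and to Table 1.

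Define the contrast as CT+IPT versus waiting list on the 8-week BDI-II in all randomised patients, adjusted for baseline BDI-II and for the first/recurrent stratum. Use session and month-3 scores to support the handling of missing week-8 values. No process scales need to be added.

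The cost is one extra 21-item web questionnaire for 150 patients and a protocol amendment. If the assessment cannot be added, the fallback is to specify in advance the window and model for the session and month-3 scores and the handling of non-attenders, and to state that the week-8 active mean then rests on those assumptions.

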### Recruitment

Participants will be recruited during regular intakes at our clinical site, the Academic Community Mental Health Centre (RIAGG) Maastricht. The SCID-I will be administered to assess current and lifetime episodes of Axis I disorders [59]. Patients meeting the inclusion criteria will be approached for participation. If they agree to participate, the SCID for Axis II disorders (SCID-II) will be administered as well [64]. After inclusion, the participants' GP will be informed about his or her participation in the study. Participants who do not meet the inclusion criteria will be offered suitable alternative treatment options.

### Randomisation and procedure

Eligible participants will be contacted by telephone for a baseline visit at the university. Preceding this initial visit to the research centre, participants will receive an appointment letter, including study information. This will allow them to consider their study participation well before they agree to participate (approximately one week). Furthermore, to decrease the burden of the first assessment, participants will be asked to already fill out a substantial part of the baseline questionnaires at home. Randomisation will take place after informed consent is obtained and the second part of the baseline questionnaires are filled out. In our design we prestratified groups by first (1 episode) and recurrent (> 1 episodes) depression. The researcher will press the 'assign' button on the computer screen, after which the database randomly allocates the participant to one of the treatment conditions (CT or IPT), or to the waiting list condition by using block randomisation. This waiting list condition is included because it has been frequently argued in psychotherapy research that the effect in treatment studies cannot be attributed to the intervention(s) that are studied, unless a placebo or no-treatment group is included [65]. With regard to the nature of the treatments, blinding of the participants and researchers is not possible.

In reporting the follow-up period of the CT and IPT condition in this study, we distinguish three phases; (a) the Treatment phase (baseline to 7 months); the period when therapy will be delivered; (b) The Trial follow-up phase (month 8-12) in which depression severity will be measured monthly; and (c) The Long-term follow-up phase (12 to 24 months); the period covered by retrospective assessment. All questionnaires will be administered on a computer. Pre- and post treatment assessment (baseline and 7 months) will take place at the University. All other follow-up self-report assessments will take place at home via the internet at three, eight, nine, ten, eleven, twelve and twenty-four months after inclusion.

Although the baseline assessment is the same, the follow-up period of the waiting list condition is somewhat different as compared to the CT and IPT condition (see Figure 1). Participants in this condition will be measured less often, and at different points in time. The treatment phase of the participants in this condition does not start immediately after baseline, but after an 8-week waiting list period. To be able to investigate the effect of this waiting period, and to mark the starting point of the treatment phase, a second identical baseline assessment will take place two months after the initial baseline assessment. As a consequence, the post-treatment assessment in this condition will take place after nine months (instead of after seven months in the CT and IPT condition). Furthermore, patients in this condition will only have two more assessment after their post-treatment measure. This will take place at 14 and 26 months, and is identical to the 12 and 24 months assessment of the CT and IPT condition. To summarize, patients in the waiting list condition will have the same baseline assessment as compared to participants in the CT and IPT condition. However, they will have a second baseline assessment at two months follow-up, and their 9, 14, and 26 month follow-up assessments will parallel respectively the 7, 12, and 24 months assessments of the CT and IPT group (see table 1).

**Table 1 T1:** Overview of instruments per time point in the CT and IPT group*

Instrument	0**	3	7	8-11	12	24
						
*Clinical Outcome measures*						
Beck Depression Inventory II	**•**	**•**	**•**	**•**	**•**	**•**
Quick Inventory of Depressive symptoms	**•**				**•**	
Brief Symptom Inventory	**•**		**•**		**•**	**•**
Diagnostic Interview for Depression		**•**	**•**	**•**	**•**	**•**
Beck Hopelessness Scale	**•**		**•**			
Longitudinal Interval Follow-up Evaluation						**•**
						
*Process variables*						
Attributional Style questionnaire	**•**	**•**	**•**		**•**	
Dysfunctional Attitude Scale	**•**	**•**	**•**		**•**	
Inventory of Interpersonal Problems	**•**	**•**	**•**		**•**	**•**
Leiden Index of Depression Severity	**•**	**•**	**•**			
Ruminative Response Scale NL	**•**	**•**	**•**			
Self-Liking and Self-Competence Scale	**•**	**•**	**•**			
Single Category Implicit Association Task	**•**		**•**			
						
*Economic Evaluation measures*						
Health care use Questionnaire	**•**	**•**	**•**		**•**	**•**
Productivity and Disease Questionnaire	**•**		**•**		**•**	**•**
Work and Social Adjustment Scale	**•**		**•**		**•**	**•**
Euroqol-6D	**•**		**•**		**•**	**•**
Rand 36	**•**		**•**		**•**	**•**
						
*Other measures*	**•**					
Genetic information						
Working Alliance Inventory		**•**				
Collaborative Study Psychotherapy Rating Scale	**•**	**•**	**•*****			
Working Alliance Inventory-short observer version	**•**	**•**	**•*****			

* Patients in the waiting list condition will receive the same baseline assessment, they will have a second baseline assessment at 2 months follow-up, and their 9, 14, and 26 month follow-up assessments parallel respectively the 7, 12, and 24 month assessments of the CT and IPT group. ** The following general predictors will be administered at baseline as well: demographic variables, family anamnesis, childhood experiences, life-events, reliability and expectations. *** During the treatment phase, all sessions will be videotaped. Only a random selection of tapes will be rated.

In all conditions a BDI-II will be filled out before each session during the treatment phase. After the two-year follow-up period, a modified version of the semi-structured Longitudinal Interval Follow-Up Evaluation (LIFE) [66] will be administered to retrospectively map out the course of depressive symptoms. To optimize the adherence of self-report assessments, participants will receive an email foregoing each assessment point. If one does not complete the questionnaires within one week, an email-reminder will be sent. If the participant still fails to fill out the questionnaires, a phone call will be made.

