### Main research questions and Hypotheses

The following main research questions were formulated:

• Are CT and IPT effective interventions in treating the acute phase of MDD and is one therapy superior to the other?

• What are the underlying psychological mechanisms of change in CT and IPT and are these mechanisms therapy-specific?

• Are CT and IPT effective in preventing relapse or recurrence of MDD in the long-term? Is one therapy superior to the other, and if so, how can these preventive effects be explained?

In line with previous research, it is hypothesized that the amount of change in depressive symptoms after therapy will be similar in both the CT and the IPT group, indicating that both treatments are just as effective in treating depression in the acute phase [14,24,56,57]. Because both therapies originally stem from different theoretical backgrounds, we expect that both treatments target depression through different key processes. It is expected that changes in cognitive schemas, attitudes, and cognitions are the most significant contributors to symptom change in CT, whereas in IPT it is assumed that improvement of interpersonal functioning will lead to a reduction of symptoms [12,16]. With regard to the mechanisms of change, many hypotheses are possible, especially when it comes to the order of change and causal pathways that lead to recovery. Following the theories one would expect that change in cognitions (CT) and interpersonal functioning (IPT) precede symptom change. Furthermore, we expect that it is the direct comparison of explicit versus implicit measures that will elicit new insights into the underlying mechanisms of change. To the extent that implicit measures reflect uncontrollable, unaware and fast mechanisms, they can provide useful additional information as compared to explicit measures. As to the prevention of relapse, we hypothesize that both CT and IPT may reduce the risk of relapse and recurrence in the long term. However, we expect CT to prevent relapse to a greater extent, because it has shown to have an enduring effect that extends beyond the end of therapy, while IPT so far only seems to be effective in treating depression as long as the treatment is continued [58].

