### Interventions

The interventions will be offered at the Academic RIAGG Maastricht. At this site, CT and IPT are already delivered as treatment as usual. Interventions are written out in a treatment manual, and both treatments will contain 12 to 20 sessions of 45 minutes, depending on the individual progress of patients. Interventions will be delivered by qualified therapists, who were trained by [name] (CT) and [name] (IPT), experts in the field of depression treatment. To prevent contamination of treatment conditions, participating therapists will deliver either CT or IPT. Therapists will consult each other on current cases in biweekly consultation meetings. The CT protocol is based on the manual by Beck (1979) and is modified for the current study with a special focus on relapse prevention. IPT is based on the manual of Klerman, Weissman, Rounsaville, and Chevron (1984). CT and IPT differ in terms of target (cognitions and behaviour vs. interpersonal functioning), approach (directive vs. empathic-reflective) and method (homework assignment vs. no assignments) [27]. All sessions will be videotaped, and a random selection of tapes will be analysed by independent assessors on treatment adherence (content and quality) by using the Collaborative Study Psychotherapy Rating Scale - version 6 (CSPRS-6) [67], and on quality of therapeutic alliance using the Observer version of the Working Alliance Inventory-Short (WAI-O-S) [68-72].

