### Analyses

Data-analysis will include intention-to-treat analyses, per-protocol analyses, change analyses and prognostic analyses. Analyses will include elementary head-to-head comparisons of the intervention groups as well as more complicated multivariate analyses (e.g., individual time series analysis, logistic regression analysis, multilevel analyses). Furthermore, in ancillary analysis, subgroups of the study sample according to symptom severity and DSM-IV classification will be examined for differential effects. In addition, we will determine the proportion of patients that show reliable and clinically significant improvement on the outcome measures. Our calculations will be based on the method of Jacobson and Truax [130] which prescribes that Clinical Improvement (CI) is based on both Reliable Change (RC), the extent to which the pre-to-post-difference score is reliable; and on Clinical Significant change (CSC), the extent to which post-treatment scores are clinically meaningful [131]. We will use chi-square tests to test the frequency differences in the RC, CSC, and CI between the three intervention groups.

Relapse (episode of MDD after remission) and recurrence (episode of MDD after recovery) in the course of follow-up (12 and 24 months) will be assessed using survival analysis (Cox proportional hazards regression). Furthermore, using multi-level mediation models, we will investigate various potential treatment mediators (psychological processes responsible for therapeutic change) to identify mechanisms of change. We will use the revised and expanded McArthur guidelines with a central focus on the temporal aspect [40,41]. Furthermore, we will use structural equation modelling to test the relative strength of the factors involved (path analysis), an approach already successfully applied by Oei and colleagues [48].

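### The chi-square tests fixed for the improvement rates leave out the randomisation stratum, baseline BDI-II as a covariate, and the therapist, who is nested in arm

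*Protocol article*

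**What the plan says.** All places are in the protocol article.

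- **Randomisation and procedure:** "In our design we prestratified groups by first (1 episode) and recurrent (> 1 episodes) depression". Allocation is by block randomisation after the baseline questionnaires. Table 1 lists the BDI-II at baseline.
- **Interventions:** to avoid contamination, "participating therapists will deliver either CT or IPT". Neither the number of therapists nor the caseload is given.
- **Analyses:** "We will use chi-square tests to test the frequency differences" in reliable change (RC), clinically significant change (CSC) and clinical improvement (CI) between the three groups. RC is built from the pre-to-post difference, CSC from the post-treatment score, and CI from both.
- **Analyses:** relapse and recurrence "will be assessed using survival analysis (Cox proportional hazards regression"), with no list of covariates, strata or clustering terms. Logistic regression and multilevel analyses appear as examples of further methods, and multilevel models again for mediation. Their levels and covariates are not stated.
- **Sample size:** 75 patients per active arm, two-sided α of 0.05, 80% power, for a relapse difference between CT and IPT. No therapist clustering or design effect is mentioned.

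**The concern.** The chi-square test is a named choice, so a fuller plan would have to replace it and could not merely add detail to it. It takes no covariates and assumes that patients are independent.

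Two issues follow and should be kept apart because they run in opposite directions.

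1. **Stratum and baseline.** If first versus recurrent episode or baseline severity predicts improvement, an analysis without them is valid but slightly conservative, and some power is lost. In a logistic or Cox model, adjustment does not shrink the standard error. It moves the estimate away from the null, and the power gain comes from there.
2. **Therapist.** Each therapist treats in one arm only, so CT versus IPT is also a comparison between two sets of therapists. If therapists differ in their results, those differences do not cancel, and an analysis that ignores them understates the standard error. A few strong or weak therapists in one arm could then look like a treatment difference, and whether one therapy is superior is a main research question.

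**Working it through.** **Step 1: the plan's own figure, and whether it leaves room for clustering.** Sample size gives "a mean relapse/recurrence rate of 33% after two years of follow-up, compared to 67% following antidepressant medication and/or clinical management", and then "we assume a difference of 20% in relapse between CT and IPT". Since "we expect CT to prevent relapse to a greater extent", I read this as 33% (CT) versus 53% (IPT).

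- Hazard ratio under proportional hazards: ln(1 − 0.33) / ln(1 − 0.53) = 0.530. Mean event risk: (0.33 + 0.53) / 2 = 0.43.
- Schoenfeld, two-sided 0.05, 80% power: 79 events; 79 / 0.43 / 2 = 92 per arm. Freedman: 84 events; 84 / 0.43 / 2 = 98 per arm.
- At 75 per arm the expected events are 75 × 0.86 = 64.5, and power is 72% (Schoenfeld) or 69% (Freedman).

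So 75 is not reproduced in the hypothesised direction with a two-sided test. It does appear with a one-sided test (73 to 77 per arm), or with Freedman's formula for 33% versus 13% (74 per arm). That mismatch is a separate matter. Here it shows only that, on this reading, the sample size has no hidden margin for a design effect.

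**Step 2: therapist.** Design effect DE = 1 + (m − 1) × ICC, where m is patients per therapist. If the test ignores clustering, the true two-sided type I error is 2 × [1 − Φ(1.96 / √DE)], and the effective number per arm is 75 / DE. Both m and ICC are assumed.

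| m | ICC | DE | SE too small by factor √DE | True α | Effective n per arm |
|---|---|---|---|---|---|
| any | 0 | 1.00 | 1.00 | 5.0% | 75 |
| 8 | 0.02 | 1.14 | 1.07 | 6.6% | 66 |
| 10 | 0.05 | 1.45 | 1.20 | 10.4% | 52 |
| 15 | 0.05 | 1.70 | 1.30 | 13.3% | 44 |
| 15 | 0.10 | 2.40 | 1.55 | 20.6% | 31 |

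These figures apply to the one-degree-of-freedom CT-versus-IPT contrast and not to the overall three-group test. As a guide to the relapse endpoint, putting 64.5 / DE events into Schoenfeld's formula turns the 72% power of Step 1 into 66%, 50% and 38% at DE 1.14, 1.70 and 2.40.

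**Step 3: stratum.** The available calculation is for relapse and not for the chi-square outcomes. It is a simulated log-rank test, 33% versus 53%, 75 per arm, with an assumed prognostic hazard ratio for recurrent versus first episode. Stratified versus unstratified power was 0.721 versus 0.713 at hazard ratio 2 (0.8 points) and 0.731 versus 0.694 at hazard ratio 3 (3.7 points). The gain is small.

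**Step 4: baseline BDI-II.** RC already uses baseline through the difference score, and CI uses it through RC. CSC rests on the post-treatment score. Baseline is therefore not wholly unused, but it is not a covariate in any of the three tests.

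**The case against.** The strongest reply is that this is a condensed article. Covariates, strata and random-effect levels are normally left to the full plan, and their absence is no error. That stands for the Cox analysis. A reader might infer that the relapse model ignores stratum, baseline and therapist, but the text never says so. Cox regression can carry covariates, strata, a frailty term or a robust variance. The article also names logistic regression and multilevel analyses, and an unspecified level is not an excluded one. The reply does not reach the chi-square tests, because there the method itself is fixed.

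A reader might also infer a large precision loss from leaving out baseline BDI-II. With an assumed correlation of 0.5, residual variance falls by 25%, as if there were 75 / 0.75 = 100 patients per arm. That formula holds for a continuous BDI-II outcome. It does not apply to chi-square or Cox analyses, and the article fixes no unadjusted test of continuous BDI-II to which the loss could be attached.

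Three further points stand:

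- The chi-square tests are introduced as additional analyses, cover three groups including the waiting list, and do not drive the sample size.
- The therapist inflation cannot be derived from the documents and vanishes at ICC 0.
- For relapse, only patients who remit are at risk. Taking the response rate of up to 60% in the Background as a rough guide, m of 8 to 15 becomes 4.8 to 9. With ICC 0.02 to 0.10 the design effect is then about 1.08 to 1.8 and the true α about 6% to 14%, before any allowance for censoring.

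**Conclusion.** The point holds for the chi-square tests of RC, CSC and CI. As fixed, they leave out the randomisation stratum, do not use baseline BDI-II as a covariate, and ignore that therapists are nested in arm.

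- **Power:** some is lost by leaving out stratum and baseline. The one figure available, for a stratified log-rank test, is about 1 to 4 points under assumed hazard ratios of 2 to 3. The loss for the chi-square outcomes themselves has not been quantified.
- **Type I error for CT versus IPT:** 5% to about 21%, for 8 to 15 patients per therapist and ICC 0 to 0.10. Both inputs are assumed, and there is no inflation at ICC 0.

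The two effects should not be netted into one statement. The documents do not support saying that the Cox analysis omits these terms. For relapse the point is a recommended improvement.

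**What to change.** 1. Replace the chi-square tests for RC, CSC and CI with logistic regression that includes first/recurrent stratum and baseline BDI-II.
2. In the CT-versus-IPT contrast, account for therapist by a random effect or by cluster-robust standard errors with a small-sample correction. Report the number of therapists per arm and the therapist ICC.
3. As an improvement, stratify the Cox model by first/recurrent depression and add a therapist frailty or a robust variance clustered on therapist.

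The change is one of analysis wording. Stratum and baseline BDI-II are already collected, and therapist identity should be known at the single treatment site.

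There is a statistical cost. CT-versus-IPT intervals widen if therapists differ, possibly by a lot: at a design effect of 2.4 the standard error is √2.4 = 1.55 times as large. With few therapists per arm, frailty or cluster-robust estimates may be unstable, so the plan should name a fallback in advance.
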